## Abstract

**Purpose:**

A protective loop ileostomy is the most useful method to reduce sequelae in the event of an anastomotic leakage (AL) after rectal cancer surgery. However, it requires an additional stoma reversal surgery with its own potential complications. Postoperative ileus (POI) remains the most common complication after ileostomy reversal, which leads to an increase in morbidity, length of hospital stay (LOS) and overall healthcare costs. Several retrospective studies carried out in this field have concluded that there are insufficient evidence-based recommendations about the routine application of preoperative bowel stimulation in clinical practice. Here we discuss whether stimulation of the efferent limb before ileostomy reversal might reduce POI and improve postoperative outcomes.

**Methods:**

This is a multicentre randomised controlled trial to determine whether mechanical stimulation of the efferent limb during the 2 weeks before the ileostomy reversal would help to reduce the development of POI after surgery. This study was registered on Clinicaltrials.gov (NCT05302557). Stimulation will consist of infusing a solution of 500 ml of saline chloride solution mixed with a thickening agent (Resource^©^, Nestlé Health Science; 6.4 g sachet) into the distal limb of the ileostomy loop. This will be performed within the 2 weeks before ileostomy reversal, in an outpatient clinic under the supervision of a trained stoma nurse.

**Conclusion:**

The results of this study could provide some insights into the preoperative management of these patients.

## Introduction

The use of a derivative loop ileostomy is an effective method recommended to mitigate potential severe intra-abdominal sepsis caused by an anastomotic leakage (AL), one of the most dreaded complications after colorectal surgery [1–5]. This procedure is commonly performed after a low anterior resection (LAR) with total mesorectal excision [6]. Reversal of the ileostomy means a second planned surgery, in which the rate of postoperative complications varies from 11% to 45% [7, 8]; of these complications, postoperative ileus (POI) is the most commonly observed with an incidence as high as 32% [9–15].

After the formation of an ileostomy, many structural and functional changes occur in the defunctionalized bowel, and these changes may contribute to the development of POI [16]. Thus, some studies have suggested that preoperative stimulation of the excluded bowel segment may positively impact the outcomes after ileostomy reversal [17], by changing the microbial dysbiosis and atrophy. These changes will improve the absorptive and motor function of the bowel before restoring intestinal continuity, thereby reducing the incidence of POI [17, 18].

Although different modalities of stimulation of the stoma have been described, there is a lack of evidence regarding which one is best, how to best perform it, and how long this stimulation should be performed [19, 20]. Thus, the main purpose of this study is to assess whether the stimulation during a 2-week period before the reversal would reduce the incidence of POI. We will analyse and compare short- and mid-term results, complications, length of hospital stay (LOS) and functional outcomes of patients with and without preoperative stimulation.

## Patients and methods

### Eligibility criteria and sample size

We have designed a multicentre, non-blinded randomised controlled trial. The inclusion criteria will be (1) adult patients (over 18 years old) undergoing elective surgery for a loop ileostomy reversal due to a previous LAR for rectal cancer; (2) all patients should be included in a standardised protocol using a water-soluble enema to prove the absence of anastomotic complications (such as leakage or stenosis before the stoma reversal). The exclusion criteria will be patients undergoing any other surgical procedure at the time of the reversal, patients with a stoma for reasons other than rectal cancer or patients with previous surgeries performed involving the distal ileum.

The designated surgeons at each participating centre will recruit potential patients to the study. At the time of planning the ileostomy reversal, all patients will be informed about the aim of the study, its possible benefits, secondary risks and the stimulation treatment protocol. Signed informed consent will be obtained from every individual patient included in the study. Participation in the study will not affect any other treatment considerations.

After inclusion in the study, patients will be randomised to an intervention or control group, as shown in Fig. 1. In the interventional arm, patients will undergo daily stimulation of the efferent limb of the ileostomy, starting 2 weeks prior to the date of surgery. In the control group, patients will not undergo any preoperative treatments before the stoma reversal.

**Fig. 1 Fig1:**
[figure not shown]
Flow diagram showing each stage of the trial, with randomisation at a ratio of 1:1

### Randomisation

Randomisation will be performed in a 1:1 ratio in each hospital using the Sealed Envelope^©^ randomisation service program. Patients will be randomised either to the interventional or control group after obtaining their consent. The attending surgeon will then be informed of the patient’s treatment group. The researcher will not know the assigned group when obtaining the patient’s consent because the randomisation will be performed afterwards. A flow diagram outlining the proposed study is shown in Fig. 1.

### Preoperative efferent bowel stimulation

All patients enrolled in the study will follow the same preoperative protocol. In the interventional arm, the stimulation will consist of irrigation with a mix of 500 ml of saline chloride solution and a nutritional thickener (Resource^©^, Nestlé Health Science, 6.4 g sachet). The patient will be instructed on how to perform the stimulation, and supervised by a specialist stoma nurse in an outpatient clinic setting, beginning 2 weeks before surgery. Daily stimulation by the stoma nurse will be offered for those patients not able to do it by themselves.

### Surgical procedure

Two technical options will be given to the surgeons who will perform the stoma reversals. Option A will be a stapled anastomosis. In this case, a skin elliptical incision around the stoma will be made. Dissection will be carried out until full mobilisation of the stoma is achieved, followed by an antiperistaltic side-to-side stapled anastomosis. The enterotomy should be closed with another stapled line, reinforced with resorbable suture. Option B will be a hand-sewn reversal. As previously described in option A, a skin elliptical incision around the stoma will be made, followed by dissection until full mobilisation is achieved. In this case, the surgeon will perform an end-to-end hand-sewn anastomosis.

Every centre can choose between option A or B when registering in the study, using the same technique for every included patient, regardless the group they are assigned to in the randomisation. All patients will receive the same antibiotic and antithrombotic prophylaxis, according to local hospital policy. No antibiotic treatment is expected during the postoperative period.

### Outcome parameters

The primary outcome will be the development of POIs, defined as intolerance to oral intake from the third postoperative day onwards (without clinical or radiological evidence of acute mechanical bowel obstruction) requiring placement of a nasogastric tube or associated with two of the following symptoms: nausea/vomiting, abdominal distention and/or the absence of flatus.

Secondary outcomes will include LOS, time to oral intake, time to first flatus, time to first stool, morbidity (including AL, surgical site infection—superficial or deep, urinary tract infections, pneumonia, postoperative acute kidney lesions, deep vein thrombosis, pulmonary embolism, small bowel obstruction, myocardial infarction, stroke, reoperation and mortality). The severity of surgical complications will be classified according to the Clavien–Dindo scale [21]. If multiple complications occur in the same patient, the most severe one will be considered.

Mid-term outcomes after a follow-up of 6 months will also be recorded and will include the hospital readmission rate and incisional hernia. The incidence of low anterior resection syndrome (LARS) will be assessed at 1 and 6 months after surgery, using the internationally validated LARS score questionnaire [22].

The collected variables will be age, sex, body mass index, American Society of Anesthesiologists (ASA) status, type of neoadjuvant treatment received (chemotherapy alone and/or short- or long-course radiotherapy), comorbidities (arterial hypertension, diabetes, dyslipidaemia and pulmonary disease) and baseline analytical parameters (proteins, creatinine, haemoglobin and white blood cells levels). Finally, the following intraoperative variables will also be recorded: operative time (minutes), type of anastomosis, presence of a parastomal hernia, the requirement for placement of a mesh and time from the index surgery to the ileostomy reversal.

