### Statistical analysis

A comparative analysis will be performed between the two study groups. Categorical variables will be analysed using contingency tables and chi-squared tests. Continuous variables will be examined by comparing the means using Student *t* tests and the medians with Mann–Whitney *U* tests. All factors for which the probability is *p* < 0.2 will be considered in multivariate logistic regression analyses with a semimanual backward (likelihood ratio) variable selection. Assuming an alpha risk of 0.05 and a beta risk of 0.2 (in a two-tailed test), we estimate that we will need to include 136 patients (68 in each group) in order to measure any statistically significant differences in the incidence of POI. A ratio of 0.29 in the control group and 0.1 in the intervention group will be considered and a 5% potential loss of patients is expected.

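### LARS is named only as an incidence, with no cut-off or category; comparing the questionnaire score already collected would be more precise

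*Protocol article*

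**What the plan says.** The Introduction makes function one of the planned comparisons: "We will analyse and compare short- and mid-term results, complications, length of hospital stay (LOS) and functional outcomes of patients with and without preoperative stimulation".

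Outcome parameters gives the functional endpoint in one sentence. The quantity is an incidence: "The incidence of low anterior resection syndrome (LARS) will be assessed at 1 and 6 months after surgery". The instrument is a scored one: "using the internationally validated LARS score questionnaire". No threshold is given, no category is named, and the score itself is not listed as an outcome. In the same section, length of stay and the times to oral intake, flatus and stool are listed in their natural units.

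Statistical analysis gives generic rules and does not mention LARS. For proportions: "Categorical variables will be analysed using contingency tables and chi-squared tests". For measurements: "Continuous variables will be examined by comparing the means using Student" t tests, with Mann–Whitney tests for medians. The sample size is set on postoperative ileus (POI) alone.

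**The concern.** An incidence is a proportion of patients with a condition. To obtain one from a score, the score must be cut somewhere. Patients just either side of the cut then count as different, and all patients on the same side count as alike. Under the plan's generic rules the resulting proportions would go to a chi-squared test at each visit.

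Two things are at stake. The first is precision: the trial is sized for a large effect on POI, and the functional comparison has to make do with the same patients. A moderate difference in bowel function that the score could show may be missed on proportions. The second is definition: an incidence derived from a score is not determined until the cut or category is named, and this trial is not blinded.

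**Working it through.** **Inputs from the article (Statistical analysis).** Two-sided alpha 0.05, power 80%, POI 0.29 against 0.10, 5% loss, 136 patients (68 per group).

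**Inputs the article does not give.** LARS rate, standard deviation, shape of the score distribution, cut-off, expected effect. These are assumed below and shown as ranges.

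**Step 1: the plan's own figure.** With the unpooled two-proportion formula,

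n = (1.960 + 0.842)² × (0.29 × 0.71 + 0.10 × 0.90) / 0.19² = 7.849 × 0.2959 / 0.0361 = 64.3 per group.

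Allowing for loss, 64.3 / 0.95 = 67.7, so 68 per group and 136 in all. The stated figure reproduces. It concerns POI only. After 5% loss, 136 × 0.95 = 129 patients are evaluable, about 64 per group.

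**Step 2: one cut.** For a normal score with a share p of patients above the cut c, the efficiency of the yes/no comparison relative to the comparison of means is φ(c)² / [p(1 − p)].

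| Share above the cut | Calculation | Efficiency | Loss | 129 patients work like |
|---|---|---|---|---|
| 0.50 | 0.3989² / 0.25 | 0.637 | 36% | 82 |
| 0.30 or 0.70 | 0.3477² / 0.21 | 0.576 | 42% | 74 |
| 0.20 or 0.80 | 0.2800² / 0.16 | 0.490 | 51% | 63 |

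Outside this range the loss grows: with 10% above the cut it is 66%.

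**Step 3: three ordered categories.** Efficiency is the sum over categories of (φ at the lower bound − φ at the upper bound)² / category share.

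- Shares 0.33, 0.34, 0.33: 0.3621²/0.33 + 0 + 0.3621²/0.33 = 0.795, a loss of about 20%.
- Shares 0.30, 0.20, 0.50: 0.3477²/0.30 + 0.0512²/0.20 + 0.3989²/0.50 = 0.734, a loss of about 27%.

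Three other splits fall between these. The figures need a test that uses the order of the categories. An ordinary chi-squared test does not, so the saving is not assured under the stated rule.

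**Step 4: what this means for power.** With 64 per group, two-sided 0.05, a normal score and a control share above the cut of 0.3 to 0.7:

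| Shift in the score | Power on the score | Power on yes/no |
|---|---|---|
| 0.5 SD | 81% | 51–61% |
| 0.4 SD | 62% | 37–43% |
| 0.3 SD | 40% | 23–27% |

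For example, at 0.5 SD the score gives a standardised difference of 0.5 × √(64/2) = 2.83, and 2.83 − 1.96 = 0.87, which corresponds to 81%. Shares of 0.30 and 0.49, which the same shift produces, give 60% by the two-proportion formula. The range of shares is symmetric about one half, so it covers shifts in either direction.

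**The case against.** A reader might infer that the plan splits LARS into yes and no, throws the score away, and so discards a third to a half of the information. The article does not support that. It never says present or absent, gives no cut-off, and does not say that the score goes unanalysed. The chi-squared rule applies only if LARS is treated as categorical. The next rule in Statistical analysis offers t tests and Mann–Whitney tests, which would fit a score without any change of method. This is also a condensed article, and a fuller protocol or analysis plan may define the categories and analyse the score.

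The size of the loss is equally conditional. It rests on normality and an assumed LARS rate, falls to 20–27% with three ordered categories, and does not apply as stated to a skewed score. No power is claimed for LARS, which is not the primary outcome, and an incidence is easier for clinicians to read.

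All of this stands, and it limits the point. It does not remove it. The article does choose a form for this endpoint, the form it names is a proportion, and function is a stated aim. A more precise comparison of the same data is available.

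**Conclusion.** The point holds as a modest improvement to a non-primary outcome, not as an error that threatens the trial. As worded, the plan names an undefined incidence where a score is available, and its rule for proportions would lead to a chi-squared test.

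If the comparison rests on a single cut of a roughly normal score with 20–80% of patients above it, the cost is about 36–51% of the information. If three categories are used and their order is respected, it is about 20–27%. Which of these applies, if either, cannot be settled from the article, so neither should be quoted as the loss in this trial. The POI comparison and its sample size are untouched.

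**What to change.** Add one sentence to Outcome parameters or Statistical analysis: the LARS score is the variable compared between arms at 1 month and at 6 months, by the Mann–Whitney or t test already in the plan, with an effect estimate and 95% CI. A repeated-measures model over the two visits is optional. Keep the incidence as a supporting summary, and state the category or cut-off that defines it before the data are examined.

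This needs no new data, visits or patients. The one drawback is that a difference in score is less familiar to clinicians than an incidence, which is why the incidence should still be reported alongside it.

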### Statistical analysis

A comparative analysis will be performed between the two study groups. Categorical variables will be analysed using contingency tables and chi-squared tests. Continuous variables will be examined by comparing the means using Student *t* tests and the medians with Mann–Whitney *U* tests. All factors for which the probability is *p* < 0.2 will be considered in multivariate logistic regression analyses with a semimanual backward (likelihood ratio) variable selection. Assuming an alpha risk of 0.05 and a beta risk of 0.2 (in a two-tailed test), we estimate that we will need to include 136 patients (68 in each group) in order to measure any statistically significant differences in the incidence of POI. A ratio of 0.29 in the control group and 0.1 in the intervention group will be considered and a 5% potential loss of patients is expected.

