### Trial status

Twenty-four centres in Spain are currently recruiting patients. The approximate end of the recruitment period will be March 2024. This study has been registered on Clinicaltrials.gov (NCT05302557) and the protocol has been structured following the Standard Protocol Item: Recommendations for Interventional Trials (SPIRIT 2013) checklist [23].

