Some risk factors for POI have been identified in previous studies, such as hand-sewn anastomoses and delayed reversal (more than 10 months after the rectal resection) [25–28]. Other studies have found that patients with chronic kidney disease and those who suffered any complications after primary surgery have a higher risk of developing postoperative complications [24–27]. POI may occur because of atrophy of the villi and muscular layers in the excluded segment of bowel, as well as a loss of contractility. In this sense, Abrisqueta et al. proposed that preoperative bowel stimulation via the efferent limb may reverse some of these changes [17]. They conducted a prospective randomised study that demonstrated reduced rates of POI among patients with efferent loop stimulation. This procedure seemed to activate cellular absorption mechanisms, facilitating the return to normal bowel function, with the time required to re-establish oral transit and ingestion being shorter. Some additional benefits such as postoperative comfort, a reduction in LOS and lower healthcare costs were also identified [17, 18].

Several ways to stimulate the distal bowel have also been assessed [19, 28–30]. Physiological stimulation with the patient’s own faeces could provide an alternative way of stimulating defunctionalized bowel, thereby combining both mechanical stimulation with benefits related to the innate microbiota [31]. In this study, saline solution will be employed instead of intestinal contents. Although the latter is more physiological, it could represent a more complex procedure for patients to perform by themselves.

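### POI is to be compared with an unstratified chi-squared test although randomisation is within hospital and hospital fixes the anastomotic technique: a valid test, but conservative if hospitals differ materially

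*Protocol article*

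**What the plan says.** Four statements in the protocol article bear on this point.

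- **Allocation** (Randomisation): "Randomisation will be performed in a 1:1 ratio in each hospital". Hospital is therefore the allocation stratum. No block size is given.
- **Technique** (Surgical procedure): "Every centre can choose between option A or B when registering in the study". The chosen technique, stapled or hand-sewn, then applies to all of that centre's patients in both arms. Technique is nested in hospital and known before any patient is randomised.
- **Prognosis** (Discussion): the risk factors for POI reported by earlier studies include some "such as hand-sewn anastomoses and delayed reversal". Chronic kidney disease and complications after the primary surgery are then named as raising the risk of postoperative complications. No effect sizes are given.
- **Analysis** (Statistical analysis): "Categorical variables will be analysed using contingency tables and chi-squared tests". POI is binary, so this is the only test stated for it. A logistic regression follows, with factors screened at p < 0.2 and then removed by semimanual backward selection.

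Centre is not in the list of collected variables under Outcome parameters; type of anastomosis is. On the number of hospitals, Trial status says: "Twenty-four centres in Spain are currently recruiting patients".

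**The concern.** When allocation is balanced within hospitals, differences in POI between hospitals largely cancel out of the comparison of arms. The pooled chi-squared test nevertheless counts those differences as noise. Its variance uses the overall p(1 − p), which is the average within-hospital variance plus the variance of the hospital rates. Only the first part should count under blocked within-hospital allocation. The test statistic is then too small on average and the test rejects less often than its nominal 5%.

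The protocol gives a reason to expect hospitals to differ, because each one fixes a technique that the protocol itself links to POI. Some efficiency that the randomisation scheme makes available is then left unused. The logistic regression does not reliably recover it: centre is not named, and whether technique stays in the model depends on the data.

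**Working it through.** **1. The plan's own figure.** Inputs from Statistical analysis: two-sided alpha 0.05, beta 0.2, an allowance of 5% for loss, and these rates: "A ratio of 0.29 in the control group and 0.1 in the intervention group will be considered".

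- Pooled-variance formula, with mean rate (0.29 + 0.10)/2 = 0.195: n per group = [1.960·√(2·0.195·0.805) + 0.842·√(0.29·0.71 + 0.10·0.90)]² / 0.19². This rounds up to 68, so 136 in total before any loss.
- Unpooled formula: (1.960 + 0.842)²·(0.2059 + 0.0900)/0.0361 = 64.3 per group. Allowing for 5% loss, 64.3/0.95 = 67.7, which rounds up to 68, so 136 with the loss included.

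Either route reproduces 136, and both are unstratified two-proportion calculations. That supports reading the plain chi-squared test as the intended comparison for POI.

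**2. Patients per hospital.** 136/24 = 5.7 on average. With 5% loss, 68·0.95 = 64.6, or about 65 per arm and 130 evaluable.

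**3. What must be assumed.** The protocol gives no between-hospital variation, no effect size for technique, no block size and no hospital sizes. The simulations assume permuted blocks of 4 within hospital and a normal hospital effect on the logit scale with standard deviation (SD) from 0 to 1.5. Where technique has an effect, its odds ratio (OR) is 2. For scale, hospitals one SD above and below average differ by an OR of exp(2·SD): 2.7 at SD 0.5, 7.4 at SD 1.0 and 16.4 at SD 1.4.

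**4. Chi-squared against Cochran-Mantel-Haenszel (CMH) over all 24 centres.** 136 patients, no technique effect, 4,000 replicates. Monte Carlo standard error is about 0.3 points for size and 0.6 for power.

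| SD | Size, chi-squared | Size, CMH | Power, chi-squared | Power, CMH |
|---|---|---|---|---|
| 0 | 4.6% | 4.6% | 82.1% | 80.5% |
| 0.5 | 4.8% | 5.1% | 82.6% | 81.7% |
| 1.0 | 3.5% | 4.3% | 82.4% | 84.4% |
| 1.5 | 2.8% | 4.8% | 82.7% | 87.7% |

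The chi-squared test stays below 5% throughout and becomes conservative as hospitals diverge. Stratifying by all 24 centres costs power when they are alike, because many small centres contribute nothing (about 8 of 24 at SD 0 under the planned rates).

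**5. Chi-squared against the test proposed here.** This is CMH by centre, with centres of fewer than 8 patients pooled within technique. 130 patients, 4,000 replicates. About 18 of the 24 centres fall below 8 and are pooled.

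| SD | Technique OR | Power, chi-squared | Power, pooled CMH | Difference (points) |
|---|---|---|---|---|
| 0 | 1 | 80.3% | 80.0% | −0.3 |
| 0.5 | 2 | 80.8% | 81.0% | +0.2 |
| 1.0 | 2 | 82.1% | 84.0% | +1.9 |
| 1.4 | 2 | 81.1% | 84.4% | +3.3 |

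A separate run of the same comparison gave 79.7% against 79.4% with no centre effect, again a cost of 0.3 points. In that run the chi-squared test's size was 4.0% at SD 1.0 and 2.8% at SD 1.4, and the pooled test's size was closer to 5%.

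**The case against.** The strongest reply is that nothing is invalid. Arms are balanced within hospital and hence within technique. A reader might infer confounding by technique or an inflated false-positive rate; the design rules out the first, and the simulated size of the chi-squared test stays at or near 5% or falls below it. A reader might also infer that the trial loses power it had planned for. It does not: the chi-squared test keeps essentially its planned 80% in every scenario. This stands and limits the point to efficiency.

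The gain also rests on undocumented inputs. It appears only at large between-hospital variation, and the conservatism needs allocation that is actually restricted within hospital. With unblocked allocation the chi-squared test held its nominal size (4.6 to 5.2%). This stands as a condition. Allocation described as 1:1 in each hospital makes blocking the likelier reading, but the article does not confirm it.

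Two further objections carry less weight. Technique may enter the logistic regression, since type of anastomosis is recorded. That is true, but its entry depends on data-driven selection, and centre is not named. It can also be said that a condensed article leaves stratified analysis to the statistical analysis plan, and that the chi-squared sentence is generic and not labelled as primary. The label is indeed absent. But the article does name a test, it is the only one that covers POI, and it matches the sample-size calculation. The point concerns a stated choice, not an omission.

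**Conclusion.** The point holds as a modest matter of efficiency and of matching the analysis to the design. The stated test does not use the strata within which the trial randomises. If allocation is blocked within hospital and hospitals differ materially in POI (assumed logit SD 1.0 to 1.4), the test is valid but conservative, with size about 3 to 4%, and yields about 2 to 3 points of power to the proposed test. At SD 0.5 or less the difference is negligible. The documents do not say which situation applies.

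Two stronger readings should be resisted. The gain of up to 5 points (82.7% to 87.7% at SD 1.5) belongs to CMH over all 24 centres, which loses power when centres are alike; it is not what the pooled test delivers. And the Discussion does not make technique the one strong prognostic factor: it gives no effect size and names delayed reversal in the same sentence.

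**What to change.** Prespecify, before outcome data are examined, that the primary comparison of POI is a Cochran-Mantel-Haenszel test without continuity correction, stratified by centre, with small centres (for example, fewer than 8 patients) pooled within anastomotic technique. Report the Mantel-Haenszel risk difference with its 95% confidence interval. Keep the plain chi-squared test as a sensitivity analysis, and record centre as an analysis variable.

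This takes a sentence or two of analysis text and leaves the sample size at 136. The price is about 0.3 points of power if centres and techniques do not differ.

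### The only adjusted analysis is built by a p<0.2 screen and discretionary backward selection over 18 variables plus arm, so a treatment effect taken from it would be unreliable; the unadjusted comparison is unaffected

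*Protocol article*

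**What the plan says.** The Statistical analysis section of the protocol article first plans a comparison of the two study groups, with chi-squared tests for categorical variables and t or Mann-Whitney tests for continuous ones. It then says that every factor with p<0.2 "will be considered in multivariate logistic regression analyses with a semimanual backward (likelihood ratio) variable selection". The sample size follows in the same paragraph: "Assuming an alpha risk of 0.05 and a beta risk of 0.2 (in a two-tailed test"), "136 patients (68 in each group"), and "A ratio of 0.29 in the control group and 0.1 in the intervention group will be considered".

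The candidate factors are listed under Outcome parameters. Besides patient characteristics, comorbidities and laboratory values, "the following intraoperative variables will also be recorded: operative time (minutes), type of anastomosis, presence of a parastomal hernia", followed by mesh placement and the time from index surgery to reversal. The Discussion names risk factors for POI already reported, "such as hand-sewn anastomoses and delayed reversal (more than 10 months after the rectal resection").

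**The concern.** The rule lets the trial's own data choose the covariates, and the word semimanual lets the analyst override the algorithm, so the result cannot be reproduced from the protocol. Three features matter if the model is used to judge stimulation.

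- **Arm is treated like any other factor.** As worded, it could be screened out, or kept and reported only when its estimate is extreme.
- **Some candidates arise after randomisation.** Operative time and the need for a mesh are determined at surgery, after the two-week stimulation period. Adjusting a randomised comparison for them can distort it.
- **The screen has two readings.** The p-value could be for association with POI, or for a difference between arms as in the tests just described. The second reading selects covariates on chance imbalance.

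At stake is a second answer to the main question, with a p-value somewhat too small and an odds ratio somewhat too far from 1, sitting beside the chi-squared result.

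**Working it through.** **Inputs from the article.** POI risk 0.29 (control) and 0.10 (stimulation); two-sided alpha 0.05; power 0.80; 68 per arm; 5% loss; 1:1 allocation.

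**The plan's own figure.** Pooled-variance formula, with mean risk 0.195:

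n = [1.96·√(2×0.195×0.805) + 0.842·√(0.29×0.71 + 0.10×0.90)]² / 0.19² = 67.1, so 68 per arm, 136 in total, before any loss.

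The unpooled formula gives 64.3, and 64.3/0.95 = 67.7, also 68 per arm, with the loss included. Either way the size rests on an unadjusted comparison of two proportions.

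**Expected events.** 68×0.29 + 68×0.10 = 19.7 + 6.8 = 26.5. After 5% loss: 26.5×0.95 = 25.2.

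**Candidates.** Five patient factors (age, sex, body mass index, ASA, neoadjuvant type), four comorbidities, four laboratory values and five items in the intraoperative list: 5+4+4+5 = 18, or 19 with arm. Events per candidate: 26.5/19 = 1.4. This describes the candidate pool. In the simulations below, 3.6-5.7 covariates on average passed the screen and 1.2-4.8 terms stayed in the final model.

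**Simulation.** 3,000 trials per scenario, 136 patients, 18 independent candidates (8 continuous, 10 binary), p<0.2 screen against POI, backward likelihood-ratio removal at 0.05 or 0.10, with none or three candidates truly prognostic. Monte Carlo standard error is about 0.4 points.

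| No true effect | Rejection rate |
|---|---|
| Chi-squared test | 4.5-5.1% |
| Arm in selected model, arm screened | 5.3-6.1% |
| Arm in selected model, arm forced in | 5.8-6.6% |
| Either test counted as success | 6.1-8.4% |

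A separate run gave 6.2% with arm screened and 6.8% with arm forced in, so the overall range is 5.3-6.8%.

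**Size of effect at 0.29 v 0.10.** True odds ratio = (0.29/0.71)/(0.10/0.90) = 3.68; log = 1.30. With three prognostic covariates the true conditional log odds ratio is 1.44. Median absolute log odds ratios:

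| Estimate | Median / true | Excess |
|---|---|---|
| Unadjusted | 1.34/1.30 | 3% |
| Selected model, arm forced in | 1.39/1.30 to 1.57/1.44 | 7-9% |
| Selected model, only when arm retained | 1.49/1.30 to 1.68/1.44 | 15-17% |

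**How much of the last row is selection?** Reporting only retained effects is largely a significance filter, and a plain test filtered the same way also exaggerates. Exact enumeration at 65 per arm gives the median unadjusted odds ratio among trials with a significant chi-squared test. It is set beside a simulation at 65 per arm of the model with arm retained (removal at 0.05, 18 noise covariates):

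| Risks | True | Chi-squared, filtered | Model, retained | Share of excess from filter |
|---|---|---|---|---|
| 0.29 v 0.10 | 3.68 | 4.25 | 4.6 | (4.25−3.68)/(4.6−3.68) = 62% |
| 0.20 v 0.10 | 2.25 | 3.81 | 4.2 | (3.81−2.25)/(4.2−2.25) = 80% |

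In the second row the chi-squared test has only 35% power, which is why the filter dominates there.

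**The case against.** The strongest reply is that the article never assigns this model the task of estimating the treatment effect. The section opens with a comparison of groups, POI is binary and so falls to the chi-squared test, and the sample size compares two unadjusted proportions. A sentence about all factors with p<0.2 reads like a secondary risk-factor analysis. This stands: the chi-squared comparison is the natural primary reading, and selection leaves its error rate and power alone.

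A second reply is that the removal threshold, whether arm is forced in and which analysis decides the trial are details a condensed article may leave to the full protocol or analysis plan. That also stands, so those silences are not counted as errors. What remains is the selection rule itself, which the article states outright and which further detail would have to replace rather than complete.

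A reader might infer more: that the model's p-value is invalid, that the trial's result will be grossly exaggerated, or that 1.4 events per term makes the fit meaningless. The documents and figures do not support these. The inflation under a mechanical rule is modest and its lower end is hardly distinguishable from 5%. Most of the striking odds ratios come from the significance filter. The ratio of 1.4 is not that of the fitted model. Nor does the article say the analyst is unblinded; it says only that the trial is. Of the items grouped as intraoperative, anastomosis type is fixed by centre at registration and parastomal hernia is not evidently a consequence of stimulation, so the post-randomisation point rests on operative time and mesh.

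**Conclusion.** The concern holds in a limited form. The stated rule is a poor way to obtain an adjusted treatment effect, and an estimate taken from it would be unreliable. The cost is roughly 0.3-1.8 points of type I error on a nominal 5%, a total error of about 6-8% if either test may be claimed, and a log odds ratio 7-9% too large with arm forced in, against about 3% unadjusted. The 15-17% seen when arm is reported only if retained should not be attributed mainly to selection.

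These sizes rest on assumptions outside the document: independent covariates, assumed prevalences, one term per variable, none or three prognostic factors, screening against POI, and removal at 0.05 or 0.10. Human discretion was not simulated and could make matters worse. The unadjusted comparison of POI by arm is not put in doubt. This is a cheap improvement, not a must-fix.

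**What to change.** Before data lock, revise the Statistical analysis wording as follows.

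1. Name the unadjusted comparison of POI by randomised arm as the primary analysis, reported as a risk difference and a risk ratio with 95% confidence intervals.
2. For any adjusted treatment effect, drop the p<0.2 screen and the backward selection. Use one supportive model that always includes arm and a short fixed list of pre-randomisation covariates. The Discussion supplies candidates: anastomotic technique, which each centre fixes at registration, and time since index surgery. The article records the latter up to reversal; counting it up to randomisation keeps it strictly pre-randomisation.
3. Exclude operative time and mesh from that model.
4. Label any selected risk-factor model for POI exploratory, and state that it is not used to judge stimulation.

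The cost is a few sentences, with no added patients or procedures. The downside is that a covariate not on the list cannot be added later.
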